## Abstract

The combination of chronic kidney disease (CKD) and peripheral artery disease (PAD) enhances the already present high cardiovascular risk, exposing the affected patients to unfavourable long-term clinical outcomes. Physical exercise is considered an effective treatment for reducing sedentary behaviour and improving quality of life, but several barriers limit patient participation. In this parallel-design, single-blinded, randomised controlled trial, we will enrol 130 patients with concomitant CKD at stages III and IV and PAD at the claudication stage to be randomised into a 6-month exercise (Ex) or control (Co) intervention. The Ex programme will consist of two daily 10 min interval walking sessions (1 min of walking followed by 1 min of resting), with gait speed controlled via a metronome and increased approximately weekly. The Co group will receive standard nephrological care. Outcomes will be assessed before and after treatment, as well as at the 12-month follow-up. The primary outcome will be the 6 min walking distance. The secondary outcomes will include quality of life, lower limb and handgrip strength, body composition and bone mineral density, as well as circulating indexes of kidney function and long-term clinical outcomes. Since no trials have been published that purposely enrol this high-risk population (CKD-PAD), the eventual positive results will validate a simple, pain-free exercise intervention that can be carried out at home to improve patients’ mobility and quality of life. Trial registration number: NCT06621264.

WHAT IS ALREADY KNOWN ON THIS TOPICWHAT THIS STUDY ADDSThe EXACT-CKDPAD study aims to investigate whether a simple, pain-free, home-based walking programme is feasible and effective in improving patients’ mobility, quality of life and long-term clinical outcomes.HOW THIS STUDY MIGHT AFFECT RESEARCH, PRACTICE OR POLICYIf the trial results confirm the initial hypothesis, a pain-free, simple walking programme will be made available to a wide number of patients worldwide, allowing them to carry it out at home, thereby improving their physical functioning and potentially reducing the burden on national healthcare services.

## Introduction

 Chronic kidney disease (CKD) is one of the fastest-growing non-communicable diseases. It is responsible for 1.2 million deaths per year and is projected to become the fifth leading cause of years of life lost worldwide by 2040.^1^,^3^ This high risk of morbidity and mortality^2^ is the sum of several critical factors affecting patients with CKD, who are exposed to an increased cardiovascular risk, including a higher risk of developing peripheral artery disease (PAD). In particular, PAD is related to adverse short-term and long-term clinical outcomes,^4 5^ considering the strong association between albuminuria and amputation.^6^

Approximately one out of four patients in the world with CKD is concomitantly affected by PAD.^7^ PAD prevalence in patients with reduced kidney function is significantly higher (24%) compared with subjects (3.7%) with normal kidney function (3.7%), and on the other hand, CKD prevalence is close to 40% in patients with PAD.^4^ These considerations delineate a subgroup of patients who share the same traditional risk factors (older age, diabetes, hypertension, hyperlipidaemia, smoking, physical inactivity) but also present unique risk factors, such as increased albuminuria, inflammation, oxidative stress, endothelial dysfunction and an unbalanced metabolic panel.^8 9^ These aspects are all closely linked in terms of both cause and effect to the sedentary attitude of the patient with CKD.^10^,^12^ Indeed, this high-risk population is poorly engaged in multidisciplinary secondary prevention programmes,^13 14^ and the need for effective interventions with sustainable benefits is reflected in the lack of previous randomised controlled trials (RCTs) focused on improving people’s mobility. In addition, reduced physical activity is associated with unfavourable outcomes in patients with CKD, including progressive deconditioning, poor control of risk factors, reduced muscle mass and fatigue up to sarcopenia.^12 15 16^ Exercise may counteract these effects in both CKD and PAD populations,^4 16^ and higher physical activity levels may contribute to better management of cardiovascular risk factors and, possibly, retard CKD progression.^17 18^ Indeed, several meta-analyses have been conducted in both populations, yielding promising results in terms of mobility, exercise capacity, quality of life, laboratory parameters and many other outcomes.^19^,^29^

However, despite the effectiveness of exercise and physical activity programmes, several barriers are still present for patients’ participation, both in CKD and PAD populations.^30 31^

To this end, the search for models of exercise prescription that are connectable with nephrology services should be implemented; however, no trials are available for the global management of this condition in the CKD-PAD population.^32^

In recent years, a home-based walking programme has been developed to overcome barriers to exercise among patients with CKD and PAD. It has been successfully tested with favourable effects on exercise capacity, physical functioning and quality of life in patients with CKD^33^,^35^ and PAD.^36^,^39^ We hypothesise that a very similar intervention could also be effective when both conditions are present.

Therefore, this multicentre RCT aims to test the effectiveness of a home-based pain-free exercise programme in a CKD-PAD population on mobility, quality of life, exercise capacity and long-term outcomes, including CKD progression, peripheral revascularisations and survival compared with usual care.

## Methods

### Study design and setting

This study protocol is reported following the Standard Protocol Items: Recommendations for Interventional Trials (SPIRIT) guidelines.^40^ The study is designed as a multicentre, parallel-group, single-blinded, RCT. The trial is available at Clinicaltrials.gov NCT06621264.

The study will take place at Sant’Anna University Hospital of Ferrara, which will act as the coordinating centre, as well as at Grande Ospedale Metropolitano Bianchi-Melacrino-Morelli of Reggio Calabria, Ospedale Pederzoli in Peschiera del Garda, the University of Verona and Casa Sollievo della Sofferenza in San Giovanni Rotondo. All units will cooperate in the enrolment of patients and data collection.

### Eligibility criteria

Patients will be included if the following criteria are respected: male and female patients aged >18 years affected by CKD at Kidney Disease Outcomes Quality Initiative (KDOQI) stages III or IV with concomitant PAD at Rutherford’s stages I–III; ability to walk independently; cognitive function to give informed consent identified by a Mini Mental Status Examination score≥20/30 and absence of clinical conditions contraindicating exercise therapy (eg, unstable angina, severe heart failure at New York Heart Association class IV, anaemia with Hb<100 g/L). Exclusion criteria are major amputations; major surgery planned in the next 3 months; known comorbid conditions that may limit survival to <2 years and inability or unwillingness to comply with protocol requirements.

Each Operative Nephrology Unit database will select all potential patients. If the inclusion criteria are met, potential participants will be given a study information leaflet detailing the study’s objectives, procedures, time frame, risks and potential benefits, as well as the telephone contact details of the staff involved and the Consent Form (supplementary material). Within the following week, candidates will be contacted by telephone and asked about their decision. For those who decide to participate, an appointment will be scheduled at which signed informed consent will be requested, and a baseline assessment session will be performed. The total number of subjects screened will be recorded according to the Consolidated Standards of Reporting Trials guidelines (figure 1).

**Figure 1 F1:**
[figure not shown]
Flow chart of the study.

### Interventions

Patients randomised to both groups will receive optimisation of medical therapy and standard nephrological care. Follow-up visits and assessments for each group member will be performed by a specialised physician and an exercise physiologist

#### Control group

Patients enrolled in the control group will receive standard CKD-PAD care, including optimal medical therapy and nutritional advice.

### Concomitant care and recommendations

No restrictions of concomitant care physiotherapy or physical activity programmes are applied. Any participation in exercise programmes or changes in pharmacological therapy will be precisely recorded in both groups.

### Fidelity to treatment

Several actions will be taken to maintain a high level of adherence and interest among patients enrolled in the exercise group. First, the walking programme will be explained by the physician and tried by patients during the first visit to state the feasibility and friendliness of the programme. Second, patients will be encouraged to continue participating in the programme during follow-up visits in the first and third months and will receive fortnightly phone calls from a researcher responsible for monitoring patients’ health and addressing any possible doubts or concerns. Finally, next to an optimally written scheme and explanation of the programme, a properly designed training diary will be provided to each patient to record exercise execution and any potential symptoms. Patients in the control group will also receive a diary to record the physical activity performed for each day.

### Outcomes

Outcome measures will be collected at baseline (T0), after 6 months (T1), which corresponds to the end of the training programme for the experimental group, and at the 12-month (T2) follow-up by healthcare professionals blinded to patients’ allocation.

*The primary outcome* will be the measurement of the 6 min walking distance (6MWD) performed during the 6 min walking test.^41^ The variations in mobility assessed by 6MWD will be determined at the end of the programme in relation to the baseline. The patients will be instructed to walk back and forth along a 20 m corridor, aiming to cover as much distance as possible. Patients will also have to report the onset of any symptoms during the test, and the correspondent distance will be recorded as pain-free walking distance. When necessary, they will be allowed to stop as needed and restart whenever possible. Patients will also be monitored with a pulse oximeter to check their corresponding saturation. The rate of perceived exertion will be recorded on the 0–10 Borg scale at the end of the test.

*Secondary outcomes* will include the following:

Lower limb perfusion. The haemodynamic severity of the disease will be assessed by the ankle-brachial index (ABI). This measure will be performed according to the published standards. The patient lies in a supine position, and blood pressure values at the ankle (from the posterior tibial and dorsalis pedis arteries) will be collected and compared with the systolic blood pressure. ABI is obtained by the ratio of the highest ankle value recorded and will be determined for both legs.^42^Foot perfusion and temperature will be measured using an infrared thermal camera (FlirOne Pro, Flir, Milan, Italy). Infrared thermography is a non-invasive technique which has not yet been employed systematically in clinical trials, used for easy and reliable foot perfusion detection with promising results in patients with PAD.^43^ A sample of five points covering the foot (anterior and posterior tibial, dorsalis pedis and plantar) will be measured and collected, as previously proposed in the literature.^44^The five-time sit-to-stand test will assess lower limb strength. Patients will rise from a standard-height chair with their arms folded across the chest five times as quickly as possible. The total time elapsed for completing the five repetitions is the score.^45^Handgrip strength will be measured using a standard dynamometer (Takei dynamometer). With one hand at a time, patients will be asked to perform three repetitions. The peak and mean values will be collected.Quality of life will be assessed by the Short-Form 36 questionnaire. This is a generic questionnaire that contains 36 questions referring to eight specific domains related to patient physical and mental health over the previous 4 weeks.^46^Bone mineral density will be measured through phalangeal quantitative ultrasound (QUS, DBM Sonic Bone Profiler, Igea s.r.l., Carpi) with an ultrasound signal of 1.25 MHz frequency and a methodology devoid of X-rays. QUS results are consistent with those obtained by standard DEXA.^47^ ;Body composition will be assessed with direct measures of height (cm), weight (kg) and waist circumference (cm), as well as lean body mass and lean body mass index through bioimpedance analysis (Akern, Italy).Circulating indexes of kidney function such as serum creatinine, estimated glomerular filtration rate (through the 2009 Chronic Kidney Disease Epidemiology Collaboration equation), albumin, urinary sediment and albuminuria-to-creatininuria ratio will be assessed by standard laboratory methods.Long-term clinical outcomes will also be recorded, including the number of patients requiring initiation of dialysis treatment within the 2-year follow-up period, as well as all-cause hospitalisation and mortality rates among the enrolled patients. In the event of positive findings, the number of days elapsed from enrolment to the event will be recorded for additional analysis, as well as the reasons and diagnoses. Long-term outcomes will be collected up to 3 years from the enrolment.

Participants' timeline is reported in figure 2.

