### Statistical methods

Standard methods for the analysis of RCTs will be employed. All analyses will be conducted using intention-to-treat, where any subject randomised to one arm remains in that arm regardless of whether they received the intervention.

Missing values, although we will make any effort possible to reduce their incidence, will be treated using the multiple imputation procedure. Moreover, a sensitivity analysis will be performed to assess the stability of the study’s conclusions, comparing the intention-to-treat analysis with an analysis that takes into account the level of participation in the intervention arm. A p value <0.05 will be considered statistically significant. Several statistical analysis software packages, including SPSS, MedCalc and Stata, will be used.

A Shapiro-Wilk test will verify the nature and distribution of the data. At baseline, the two groups will be compared in terms of demographics and primary and secondary outcome measures. Although our initial hypothesis suggested the superiority of the exercise group over the control group, to account for the possibility that participants in the control group might achieve better outcomes than those in the intervention arm, we will use two-tailed tests of significance for all analyses. For categorical variables, the χ^2^ test or Fisher’s test will be employed, as appropriate. Overtime between-group differences will be analysed using t-tests for symmetrically distributed data and analogous non-parametric tests, such as the Mann-Whitney test, for skewed data. A two-way repeated measures analysis of variance (factors: treatment, time) will be run to compare differences over time for secondary outcomes. Paired-sample t-tests or Wilcoxon tests will assess the within-group variations. Suppose a significantly different distribution between the two groups in the baseline outcome level is identified. In that case, a secondary analysis will be performed using multivariate modelling, such as analysis of covariance, to adjust for these factors. For the long-term outcomes, Kaplan-Meier curves with log-rank tests and Cox proportional hazard regression models will be performed.

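### Thermal-camera skin temperature is labelled foot perfusion, and within-arm paired tests of its change cannot show an exercise effect (minor, one secondary outcome)

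*Protocol article*

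**What the plan says.** Under lower limb perfusion, the Outcomes section lists the ankle-brachial index (ABI) as the measure of haemodynamic severity. It then adds a second measure: "Foot perfusion and temperature will be measured using an infrared thermal camera". The article says that thermography has not yet been used systematically in trials, but describes it as "used for easy and reliable foot perfusion detection with promising results in patients with PAD", with a citation. On sampling it says: "A sample of five points covering the foot (anterior and posterior tibial, dorsalis pedis and plantar) will be measured and collected", and refers to the literature for the choice of points.

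The visits are at baseline, 6 months (T1, end of training) and 12 months (T2).

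The Statistical methods section plans three kinds of analysis that reach this outcome:
- between-arm tests of change (t-test or Mann-Whitney);
- for secondary outcomes, "A two-way repeated measures analysis of variance (factors: treatment, time) will be run to compare differences over time for secondary outcomes";
- within each arm, "Paired-sample t-tests or Wilcoxon tests will assess the within-group variations".

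Analysis of covariance is a secondary analysis, run only if the arms differ significantly at baseline.

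**The concern.** One device is credited with two quantities. A thermal camera gives a temperature map, and the article names no separate perfusion readout, unit or conversion. Perfusion is therefore inferred from temperature. Even if the two agree well across limbs at one sitting, a change in skin temperature over six months need not be a change in blood flow.

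The label matters because of the paired tests. A rise from T0 to T1 in the exercise arm could be written up as improved foot perfusion after training. A paired test shows only that the arm's mean moved. It does not say why. Both arms receive optimised medical therapy (Interventions section), which is one reason unrelated to exercise. Season is another, because T0 and T1 lie half a year apart.

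The rule for covariance adjustment is also poorly chosen. In a randomised trial a baseline difference arises by chance, and the precision gained from adjusting does not depend on whether that difference is significant.

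**Working it through.** The article states no figure to reproduce for this outcome: no temperature SD, no seasonal size and no recruitment calendar. What follows is an illustration on declared assumptions.

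**Inputs from the article.** T1 at 6 months and T2 at 12 months (Outcomes); 48 patients per arm (Sample size and recruitment); concurrent 1:1 randomisation in permuted blocks (Allocation); two-sided 0.05 (Statistical methods).

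**Assumptions.** Foot temperature has a seasonal term -A·cos(2πm/12), with m in months from the coldest point and A = 0.25 to 1.0 °C (0.5 to 2.0 °C from coldest to warmest). The SD of change without season, s, is 1 to 2 °C. There is no treatment effect.

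**Change by visit.** A patient enrolled at month m has a seasonal T0-T1 change of 2A·cos(2πm/12). This is largest for those enrolled at an extreme and zero for those enrolled midway. The T0-T2 change is zero for everyone.

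**Mean T0-T1 shift by recruitment window.**
- 3 months centred on the coldest point: 2A·sin(π/4)/(π/4) = 2A × 0.900, or 0.45 to 1.80 °C.
- 6 months centred there: 2A × 2/π = 2A × 0.637, or 0.32 to 1.27 °C.
- 18 months starting 3 months before it: a full year cancels and a third of the window remains, so 2A × 0.637/3 = 2A × 0.212, or 0.11 to 0.42 °C.
- Even over 12 or 24 months: 0.

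A window centred on summer reverses the sign.

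**One case by hand.** A = 0.5, s = 2, 6-month window. The mean shift is 0.637 °C. The seasonal variance within the window is 4A²(1/2 - 0.637²) = 1 × (0.500 - 0.405) = 0.095. The SE is √(4 + 0.095)/√48 = 2.024/6.928 = 0.292. Then z = 0.637/0.292 = 2.18, and the chance of a significant result is about Φ(2.18 - 1.96) = Φ(0.22) = 0.59. Simulation with the t-test gave 57%.

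**Simulated rejection rates** (4,000 runs per setting; Monte Carlo SE near 5% is √(0.05 × 0.95/4000) = 0.3 percentage points):

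| Recruitment | Within-arm, T0-T1 |
|---|---|
| 3 months, winter-centred | 34-100% |
| 6 months, winter-centred | 19-100% |
| 18 months | 7-40% |
| Even, 12 or 24 months | 4.4-5.6% |

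The within-arm T0-T2 test rejects in 4.4-5.8% of runs in every setting. The between-arm test rejects in 4.5-5.7% in every setting, at both visits.

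**Noise under even enrolment.** The seasonal variance of the T0-T1 change is (2A)²/2 = 2A², so the variance ratio is 1 + 2A²/s². This runs from 1 + 0.125/4 = 1.03 (A = 0.25, s = 2) to 1 + 2/1 = 3.0 (A = 1, s = 1). The T1 value alone carries only A²/2, a quarter of 2A². A raw change score therefore handles this noise badly, and covariance adjustment lets the data choose the weight given to baseline.

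**Point count.** The text announces five points. The sites listed are anterior tibial, posterior tibial, dorsalis pedis and plantar, which makes four.

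**The case against.** The strongest reply is that the treatment question is already protected. The control arm is concurrent, the between-arm tests and the treatment-by-time analysis are planned, and season affects both arms alike. Nothing in the article says that a within-arm change would be read as an exercise effect, and the weakness of within-arm tests is common to every outcome here. All of this stands. It is why the point is minor and why the remedy concerns which analysis carries the inference.

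A reader might infer more, in four ways that the article does not support:
- **That seasonal change will be reported as improved perfusion.** This needs uneven enrolment over the calendar and feet that follow the season in an indoor assessment. The article gives neither, and with even enrolment the bias vanishes.
- **That the missing room-temperature and rest rules are an error.** An article commonly leaves these to the full protocol, and it refers to a published procedure for the measuring points.
- **That the claim of reliable perfusion detection is false.** The cited source is not at hand. What can be said is that the instrument's output is temperature.
- **That the measurement differs between centres.** One site may supply two points, or the cited procedure may fix the map. The text is ambiguous, and no more than that.

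**Conclusion.** The point holds in a limited form. The outcome is named for something that the camera does not read directly, and the planned paired tests cannot attribute a T0-T1 change to exercise. Season is one possible alternative explanation, and only under uneven enrolment. Under even enrolment it adds noise, multiplying the variance of change by about 1.03 to 3.0 on the amplitudes and SDs assumed here. The T0-T2 comparison is season-matched, and the randomised comparison between arms is not biased at either visit. Every seasonal magnitude above is an assumption and none comes from the article. The point touches one secondary outcome and leaves the primary outcome, 6 min walking distance, unaffected.

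**What to change.** 1. Name the outcome foot skin temperature, described as a surrogate of perfusion.
2. For this outcome, base inference at T1 and T2 on the between-arm difference adjusted for baseline foot temperature. Do this in all cases, not only when the arms differ significantly at baseline.
3. If within-arm paired tests are kept, present them as descriptive and do not interpret them as evidence of improved perfusion.
4. If room temperature at the visit is recorded, add it as a covariate for precision. If it is not, consider recording it.
5. Reconcile the five points with the four sites named, for example by stating which site carries two.

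Items 1, 3 and 5 are wording. Item 2 uses data already collected and costs nothing. Item 4 costs at most one extra field per visit.

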### Sample size and recruitment

The feasibility of this study is assessed by analysing the prevalence of patients with CKD-PAD in the hospitals involved in this project. We identified a cohort of over 200 patients potentially meeting the inclusion criteria. In each centre, a network of physicians, including nephrologists, internists and vascular surgeons, will be established to identify potentially eligible patients and facilitate enrolment. Every centre will identify a responsible person for enrolment to assess patients’ eligibility and manage their inclusion in the randomisation list.

We calculated the sample size, hypothesising the superiority of the experimental treatment over the control group. A sample of 96 patients, 48 in each group, is needed to detect a 30 m improvement in 6 min walking distance in favour of the experimental group, assuming an SD of improvement of 30 m, with a type I error of 0.05 and a power of 90%. To account for possible dropouts, the sample size will be increased by 30%, resulting in a total of 124 patients to be enrolled.

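### The repeated-measures ANOVA for secondary outcomes has no provision for skew, and a log-scale analysis would serve the albumin-to-creatinine ratio better than that ANOVA or the rank test

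*Protocol article*

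**What the plan says.** Outcomes lists the ratio within one secondary item on kidney function. The wording concerns measurement, not analysis: "albumin, urinary sediment and albuminuria-to-creatininuria ratio will be assessed by standard laboratory methods". The same section schedules outcome measures at baseline, 6 months and 12 months.

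Statistical methods contains four statements that bear on its analysis:

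- A distribution check: "A Shapiro-Wilk test will verify the nature and distribution of the data".
- Between-group comparisons by t-test where data are symmetric, and otherwise by "analogous non-parametric tests, such as the Mann-Whitney test, for skewed data".
- A model assigned specifically to secondary outcomes: "A two-way repeated measures analysis of variance (factors: treatment, time) will be run to compare differences over time for secondary outcomes". No exception for skewed data is attached to it.
- If the groups differ in the baseline level of an outcome, "a secondary analysis will be performed using multivariate modelling, such as analysis of covariance, to adjust for these factors". No scale is named.

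No sentence calls for a transformation, and none rules one out.

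**The concern.** A ratio of this kind cannot be negative, may differ many-fold between patients with stage III or IV CKD, and plausibly changes in proportion to its starting level. ANOVA compares arithmetic means. If it is run on such values as measured, a few patients with very high ratios supply most of the variance. The rank test removes that problem for the two-group comparison. It is not attached to the ANOVA, which is the only named model for this outcome that spans all three visits.

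CKD progression is among the aims given at the end of the Introduction, and this ratio is one of the continuous kidney markers that bear on it. What is at stake is some precision and an interpretable effect size for one secondary marker. The primary outcome is not affected.

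**Working it through.** **The plan's own figure.** There is none to reproduce. The protocol gives no effect size, variability or power for this ratio.

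**Inputs from the protocol.** 48 evaluable patients per arm, and 62 per arm at full enrolment (124/2), both from Sample size and recruitment; significance at p<0.05; two-sided tests ("we will use two-tailed tests of significance for all analyses").

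**Assumed inputs.** Log-normal values; SD of the natural-log ratio 1.0 to 2.0; within-patient correlation of log values 0.8 or 0.9; true reduction 30%.

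**Why untransformed values are a problem.** Under a log-normal distribution, a patient 2 SD above the median has exp(2 × log SD) times the median value: exp(2) = 7.4-fold at log SD 1.0, exp(3) = 20-fold at 1.5, and exp(4) = 55-fold at 2.0.

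**Log-scale power by formula.** The effect is ln(0.7) = −0.357. The SD of log change is s√(2(1−r)), and its standard error between arms is that SD × √(2/48).

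- s = 1.5, r = 0.9: SD = 1.5 × √0.2 = 0.671; SE = 0.671 × 0.204 = 0.137; z = 0.357/0.137 = 2.60; power = Φ(2.60 − 1.96) = 74%.
- s = 1.0, r = 0.8: SD = √0.4 = 0.632; SE = 0.129; z = 2.76; power = Φ(0.80) = 79%.

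The simulation below gives 73.3% and 78.7% for these two cases, so it agrees with theory.

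**Simulated power (%), 2,000 runs per row.** The standard error of each figure is at most √(0.25/2000) = 1.1 points. Gain is log ANCOVA minus Mann-Whitney on change.

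| n/arm | log SD | r | t-test, untransformed change | ANOVA, untransformed, 3 visits | Mann-Whitney on change | t-test, log change | ANCOVA, log | Gain |
|---|---|---|---|---|---|---|---|---|
| 48 | 1.0 | 0.8 | 40.4 | 42.4 | 61.6 | 78.7 | 82.3 | 20.7 |
| 48 | 1.0 | 0.9 | 63.2 | 65.2 | 88.0 | 97.0 | 97.2 | 9.2 |
| 48 | 1.5 | 0.8 | 12.4 | 10.3 | 31.8 | 45.2 | 49.7 | 17.9 |
| 48 | 1.5 | 0.9 | 20.1 | 18.6 | 53.8 | 73.3 | 74.7 | 20.9 |
| 62 | 1.0 | 0.8 | 47.0 | 50.0 | 71.6 | 87.6 | 90.4 | 18.8 |
| 62 | 1.0 | 0.9 | 71.6 | 74.9 | 94.1 | 99.2 | 99.2 | 5.1 |
| 62 | 1.5 | 0.8 | 14.0 | 13.2 | 36.5 | 55.2 | 59.2 | 22.7 |
| 62 | 1.5 | 0.9 | 25.0 | 23.4 | 63.7 | 84.0 | 85.6 | 21.9 |

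Shapiro-Wilk rejected normality of the change in every simulated trial (100% in all eight rows). The plan's own rule would therefore send the between-group test to Mann-Whitney.

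A separate run at 48 per arm that extended log SD to 2.0 gave power of 6–62% for untransformed change, 19–87% for Mann-Whitney and 29–98% for log ANCOVA. The gain over Mann-Whitney was about 10 to 23 points.

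**The case against.** The strongest reply has three parts.

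**The text never says the ratio is analysed untransformed.** This is correct. A reader might infer it from the ANOVA sentence, but that sentence names no scale. An analysis plan that is not shown may supply one, and the scale for one secondary laboratory variable is often left to such a document. What stands against this is narrower: the article does fix a model for secondary outcomes and a remedy for skew, the remedy is not tied to the model, and it is ranking, not transformation.

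**The rank rule already stops extreme values from dominating.** This is also correct for the between-group test. A reader might go further and argue that Mann-Whitney on absolute change mostly ranks how high patients started. The simulations do not support that. Signed change followed log change closely (Spearman 0.85 to 0.91) and baseline only weakly (−0.31 to −0.41). The size of the change, ignoring its sign, does track baseline (0.69 to 0.86), but Mann-Whitney ranks signed values. Likewise, differences in untransformed means pointed the wrong way in 14–16% of trials at log SD 1.5 and 28–31% at 2.0 (r = 0.9), but the Mann-Whitney statistic did so in only about 2% and 6%.

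**A null result is not made likely.** Under the rank rule, power is 88% at log SD 1.0 with r = 0.9. At log SD 2.0, where it is 32–36%, the log analysis itself reaches only about 50–55%. With a 40% reduction and r = 0.9, Mann-Whitney power at log SD 1.0, 1.5 and 2.0 is 98%, 79% and 54%.

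Two points survive: the ANOVA has no skewness provision, and the rank test gives up some power and yields no percentage effect.

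**Conclusion.** The point holds as a low-severity improvement. If the named ANOVA were run on untransformed ratios, its power would be poor: 10–75% across the tabulated cases, against 50–99% for log ANCOVA. Against the plan's own rank rule the loss is moderate, about 10 to 23 points at 48 per arm, shrinking to about 5 where rank-test power is already 94%. The ordering of the methods was the same in every case. The sizes rest wholly on assumed variability, correlation and effect, and on a log-normal shape. The protocol does not support saying that the ratio is analysed untransformed or that a real effect would probably be missed. Serum creatinine, eGFR and dialysis initiation also serve the CKD-progression aim.

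**What to change.** Add one sentence to Statistical methods: the albumin-to-creatinine ratio will be log-transformed before the between-group and repeated-measures analyses, with log baseline as a covariate whether or not the groups differ at baseline, and the treatment effect will be reported as a ratio of geometric means with 95% CI at 6 and 12 months. State the fixed constant to be used for values below the detection limit.

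The cost is small. The effect is read as a percentage change, not in absolute units, and the constant must be chosen before the data are seen. No extra patients, visits or measurements are needed. If an existing analysis plan already says this, a cross-reference is enough.
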